## Abstract

**Background:**

The DELTA intervention contains 16 weekly group sessions plus additional individual sessions and educational session for parents. It aims to reduce substance use and related problems such as substance use disorders (SUD) in adolescents. Recent results indicated positive effects in psychiatric outpatients. Conducting DELTA in youth welfare settings seems feasible, however, organizational and content adjustments such as smoking cessation elements should be added in order to reduce relapse risks and to prevent negative health consequences.

**Methods/design:**

The pre-registered DELTA-JU study (German Clinical Trials Register, DRKS00027913) is separated into three stages: In the adjustment stage during months 1–4, we will revise the DELTA manual based on semi-structured interviews (*n* = 10) with personnel from youth welfare institutions specialized in serving adolescents with SUD in the study region, analyzed with content analysis. In the sampling stage during months 5–22, participants qualifying for a SUD and willing to regularly participate in the 16 weekly DELTA-JU group sessions will be enrolled to either one of two arms (cluster randomization: immediate intervention, waitlist with subsequent intervention 16 weeks later). Adolescents will be assessed at baseline and follow-up (16 weeks after first group session) with an additional pre-assessment (16 weeks before intervention starts) for the waitlist group. Assessment procedures include questionnaires and clinical interviews among others. At the same time, institutional personnel will receive a 1-day workshop on SUD-relevant topics based on the DELTA parental education group and on feedback from the qualitative interviews. Personnel will also be assessed twice with questionnaires. In the dissemination stage during months 23–24, final study evaluation results will be prepared and submitted for publication.

**Discussion:**

This study will create a setting-specific manual for vulnerable adolescents suffering from SUDs, and, in many cases, from co-occurring mental disorders. If shown to be effective, DELTA-JU can be disseminated within other institutions of youth welfare.

## Introduction

Adolescents aged 12–18 years are likely to experiment with psychoactive substances such as alcohol and cannabis (1), with 2–10% of those who use substances developing a substance use disorder (SUD) over the course of the next years (2). SUDs are characterized as chronic mental disorders that tend to relapse into episodes of heavy substance use based on a set of biopsychosocial relapse determinants (3, 4). Such factors not only increase the risk for relapse, they are also prevalent among SUD outpatients. In our own sample of 204 outpatients (5), the majority qualified for more than one SUD (67%), had lived in single-parenthood homes (84%), repeated a class or left school prematurely (53%), or reported previous suicidal attempts (23%). Consequently, untreated SUDs are associated with delayed psychosocial development (6) and increased mortality (7, 8), thus indicating a need for prevention and treatment of SUDs.

In order to extend the existing treatment options for adolescents in Germany (9–11), we previously developed a multimodal, group-based outpatient intervention. This “Dresden multimodal therapy for adolescents with chronic substance use” (German abbreviation: DELTA) (12), consists of 16 structured weekly sessions in a group setting plus eight 1-on-1 sessions and eight additional education sessions for patients’ parents. DELTA combines recommended psychotherapeutic techniques and approaches such as motivational interviewing, contingency management, and cognitive-behavioral and systemic therapy, while also addressing mental disorders which commonly occur in addition to SUDs (5, 13, 14).

### Research directions regarding the DELTA manual

In our recent presentation of DELTA evaluation data in *N* = 146 psychiatric outpatients (including participants from youth welfare institutions), we presented first evidence that the DELTA intervention for adolescents with SUD is feasible, and shows small to medium non-significant effects in favor of DELTA regarding a reduction of both SUD severity and substance use at approximately 8 weeks after the last group session (15). Additionally, we found (small to medium) effects on the reduction of the depressive symptoms, understanding and influencing aversive emotions, and promoting prosocial behavior.

This power problem also precluded us from analyzing differences in treatment effects comparing outpatients at our outpatient unit with those who resided in a youth welfare institution and received DELTA there. Therefore, we can only assume that DELTA works the same way and leads to similar results in both settings. However, those settings differ from each other significantly. For example, in the outpatient institution, participants have to organize their commute to the group sessions while in youth welfare institutions, participants do not have to leave the building. Youth welfare institutions promote participation in group session as they schedule the group in accordance with their internal schedules, which is in contrast to the afternoon group slot in our outpatient facility which is at the same time where participants want to spend their free time with their peers. Based on these setting differences, we decided to gather additional data on DELTA in youth welfare settings where less than 33% of previously analyzed participants were treated.

#### Setting specifics in content

In our outpatient facility, adolescents may or may not yet have reached abstinence at the beginning of treatment (15). Thus, DELTA aimed at reducing substance use, achieving point abstinence, and finally achieving continuous abstinence (12). The initial sessions therefore focus on motivational techniques to reinforce commitment to achieve abstinence. In contrast, those in youth welfare institutions generally are abstinent with the start of their stay (15). In most cases they underwent inpatient detoxification before being transferred to the youth welfare institution. Thus these adolescents may already have gained SUD-related knowledge (“subjective utility”) and may already be motivated to remain abstinent rather than becoming abstinent. Not surprisingly, the evaluation study showed lowest satisfaction of adolescents with content regarding “strategies to reduce fear, to increase SUD-related subjective utility, and to reignite self-confidence in patients” (15). Therefore, it seems adequate to reframe respective sessions to fit setting-specific needs. Adolescents in these institutions live there full-time following structured routine involving psychological care, schooling, household chores, exercise, and other activities. They are under supervision continuously and are only allowed on weekends depending on their participation and commitment to institutional rules. Medical care (including psychiatric medication) is not provided by internal staff but is accessed the same ways as for other adolescents (appoints at external institutions/psychiatrists).

#### Setting specifics in stakeholder education

In the outpatient facility, adolescents present with their parents or legal guardians whom they reside with in most cases. These adults are important stakeholders in the treatment process (16, 17). Previous studies showed that parents of adolescents with SUD are both suffering from the situation but may also help to achieve treatment goals (18, 19). Thus, DELTA provided a parental education group, with eight 60-min sessions providing expert input (substances, SUD development, treatments, and family processes) as well as opportunities to reflect and discuss with other parents. In the youth welfare setting, parents do not reside with the adolescents. Although parental education settings were offered in all cooperating youth welfare institutions, the vast majority of parents generally did not attend them nor did they express interest. From a systemic perspective, institution personal plays the role of a quasi-parent in these settings. Institutional personnel may provide comparable involvement and effects in relation to the adolescent’s SUD and treatment. Thus, a revised DELTA manual should prepare similar educational sessions but for personnel. Based on feedback from the institutions during the DELTA evaluation study, such sessions cannot be attended weekly. Instead, they specifically asked for a one-day workshop to be held. Based on material for the parental education sessions a preliminary version for this workshop has been conceived, but it still requires modification based on personnel feedback.

#### Tackling tobacco smoking

Regarding the main intervention effect, i.e., reductions of use for most substances including alcohol and methamphetamine, nicotine use was an exception as it did not decrease during the follow-up period (15). As the only substance, nicotine use is partly accepted by the institutional house rules, and adolescents are permitted to smoke outside. Smoking tobacco to obtain nicotine is the most prevalent use form among our sample, with 88% of them reporting to have used tobacco in the past year on an average of 26.5 days per month (5). Tobacco use in adolescents often already starts in early adolescence (5), and lingers on although tobacco is not allowed to be purchased for persons younger than 18 years. Not only is smoking tobacco associated with detrimental consequences to health and quality of life (20), it is also regarded as a risk factor for relapse in adolescents who have reached abstinence from illicit substance use (21). Therefore, a revised DELTA manual should also focus on smoking tobacco by providing guideline-oriented aids (22).

### Study objectives/aims

In the publicly funded study DELTA-JU study (abbreviation of the German study title “DELTA in Jugendwohneinrichtungen”), we will aim: (A) to adjust sessions to the youth welfare institution setting and to needs of institutional personnel; (B) to evaluate whether the revised DELTA-JU manual is rated as acceptable by adolescent participants and institutional personnel; (C) to compliment previous results on DELTA effects, i.e., show that DELTA-JU is associated with reduced substance use (including tobacco use) and reduced SUD problems at FU.

## Methods and analysis

### Study design

Depending on their assigned condition, participants will be part of the trial for 17 or 33 weeks in total, see Table 1 for the SPIRIT schedule of enrollment, interventions, and assessments (Figure 1).

**Table 1 tab1:** SPIRIT Schedule of enrolment, interventions, and assessments.

TIMEPOINT	Study period					
	Enrollment	Allocation	Post-allocation	FU (immediate condition) BL (WL condition)	Post-allocation	FU (WL condition only)
	Week 0	Week 0	Week 1–16	Week 17	Week 17–32	Week 33
Enrolment						
Eligibility screen	X					
Informed consent	X					
Allocation		X				
Interventions						
DELTA-JU, immediate condition						
DELTA-JU, WL condition						
Assessments						
Evaluation of intervention			X	X	X	X
Substance use and SUD	X			X		X
Co-occurring psychiatric problems	X			X		X
Risk factors for substance use and SUDs	X			X		X
Cognitive functioning	X			X		X
Biological markers	X			X		X

BL, baseline; FU, follow up; SUD, substance use disorders; and WL, waitlist control.

**Figure 1 fig1:**
[figure not shown]
Overall study schedule and timeline.

To achieve the outlined aims, we conceptualized an explanatory three-stage study over the course of 24 months, see Figure 2 for the 24-month study schedule. After adjusting the DELTA manual (12), to feedback from youth welfare institution personnel (content analysis of semi-structured qualitative interviews) in the adjustment stage, participants are cluster-randomized (institution as cluster, allocation by unblinded principal investigator who assigns the group consecutively to the sequence “intervention-waitlist-intervention-waitlist”) to either one of two study arms [immediate treatment condition vs. waiting list control group condition (WL) with SUD treatment after 16 weeks] during the sampling stage. In terms of the Medical Research Council Framework for the evaluation of complex interventions (23), this design can be considered a pragmatic trial in “phase 2,” which implies that theoretically relevant aspects have been previously identified (pre-clinical research, phase 0) (12), and that components of interventional procedures are readily available (modeling research, phase 1) (12). Further elements of a pragmatic trial are a simplified analysis design and uncontrolled environments (24). Blinding of participants, care providers, outcome assessors, or analysis is not feasible in this trial. In sum, the chosen design significantly differs in several relevant aspects from ‘classical’ cluster-randomized RCT (phase 3).

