#### Sampling stage

During the sampling stage in months 5–22, adolescents will be recruited in cooperating youth welfare institutions in the study region, followed by a group-wise cluster-randomization. Adolescent participants will be prospectively assessed both at baseline (BL, a week before the intervention starts) and at follow-up (FU, 16 weeks after first group session). Those in the WL group will receive an additional pre-assessment (PRE, 16 weeks before intervention starts) for the WL to control for natural development. Assessments will take place in the youth welfare institution if possible, or in our outpatient clinic, e.g., for physical examinations. Questionnaires will be filled out in participant’s free time. Participants will be reimbursed at PRE (15 EUR), BL (20 EUR), and FU (40 EUR). The DELTA-JU group and individual sessions will be carried out as outlined below (“Interventions”) with possible changes due to the revision process. Study team members (i.e., psychologists, medical doctors, doctoral students, and student assistants from psychology, medicine, social work, or similar) who conduct the sessions or any assessment will be trained and supervised by the principal investigators.

During the same time, personnel from the youth welfare institutions will receive the revised one-day workshop on SUD-relevant topics. Workshops will be carried out either in the institutions themselves, in our outpatient clinic, in a public place, or via video conference if necessary due to restrictions for the prevention of COVID-19 infections. Whenever possible, personnel from similar institutions will be allowed to participate in the workshop. Personnel will also be assessed twice (BL at beginning and end of the workshop day, FU 16 weeks later) with questionnaires regarding the evaluation of workshop content and organization. All procedures were conducted in accordance with the Declaration of Helsinki, publicly pre-registered and approved by the local Institutional Review Board (see “Ethics” section below). For details on the dissemination stage, see "Dissemination” section below. The treatment and measurement schedule is shown in Figure 3.

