#### Waiting list control group

Participants whose group was cluster-randomized to the WL condition are not offered group sessions until 16 weeks have passed. During this period, adolescents may seek any kind of treatment as usual, including medication for co-occurring disorders or any kind of SUD treatment. Afterwards, DELTA-JU is provided in the same way as in the immediate treatment condition described above. The pre-treatment waiting period acts as a naturalistic comparator to the treatment. It is a suitable comparator given that many of the possible confounders (housing, timespan since previous detoxification treatment, availability of concurrent treatments/medication, psychosocial support, schooling situation etc.) should be equally present or absent in both conditions. Since concomitant treatments are allowed and documented in both conditions, we will be able to control for this confounder while at the same time providing a comparator group that represents the heterogeneity of SUD care in this population.

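### The trial is described as cluster-randomized, but the stated rule is strict alternation by an unblinded principal investigator, so arm comparability has no random basis

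*Protocol article*

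**What the plan says.** All references are to the protocol article.

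- **Study design** says "participants are cluster-randomized (institution as cluster" and continues the same bracket with the rule: "allocation by unblinded principal investigator who assigns the group consecutively to the sequence" "intervention-waitlist-intervention-waitlist". It adds that "Blinding of participants, care providers, outcome assessors, or analysis is not feasible in this trial", and closes by saying that the design differs in several respects from a classical cluster-randomized trial. It does not list allocation among those differences.
- **Abstract, Methods/design** describes enrolment to two arms by "cluster randomization: immediate intervention, waitlist with subsequent intervention 16 weeks later".
- **Sampling stage** has recruitment in the institutions "followed by a group-wise cluster-randomization".
- **Waiting list control group** says "Participants whose group was cluster-randomized to the WL condition are not offered group sessions until 16 weeks have passed". It then defends the waiting period as a comparator because many possible confounders, including time since detoxification, should be alike in the two conditions.
- **Setting and participants** and **Data analysis** also use the word randomized, the latter for how adolescents will be analysed.
- **Data analysis** makes the confirmatory test a within-participant time effect in all 40 analysed adolescents and treats between-group effects as unimportant.
- **Hypotheses** and **Strengths and limitations** set reductions through follow-up against the PRE-to-baseline change in the waitlist group, and present this as a way to control for other explanations of change over time.

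**The concern.** A fixed alternating order is not randomization. The person who assigns the arms is unblinded and knows the sequence, so whoever decides or influences which cluster comes next also decides its arm. The article states this rule itself; it is not a detail left to a fuller document, and further detail elsewhere would not make the stated rule random.

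Two statements lean on the arms being comparable: the argument that confounders are alike in both conditions, and the natural-course comparison. The analysis offers little repair if they are not. Strengths and limitations says that adjustment for several baseline variables is impossible at this sample size and that parallel treatments cannot enter the effect estimate.

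The unit is also unclear. Study design names the institution as the cluster and then assigns the group; Sampling stage and Waiting list control group speak of groups. If one institution supplies more than one group, these are different designs.

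**Working it through.** **1. Does the primary test depend on allocation?** Inputs from Estimation of sample size: alpha 0.05, power 0.95, f = 0.40, r = 0.1, two time points (m = 2). For a within-participant effect the noncentrality is λ = f² × N × m / (1 − r). At N = 40, λ = 0.16 × 40 × 2 / 0.9 = 14.2, which gives power 0.957. The smallest N reaching 0.95 is 39, or 40 when rounded up to two equal groups. The stated 40 is reproduced, as is the number to enrol: 40 / (1 − 0.20) = 50. The arm contrast does not enter this calculation. The sample size and the primary p-value therefore do not rest on how clusters were allocated.

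**2. How predictable is the next arm?** Share of allocations guessed correctly:

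| Scheme | Correct guesses |
|---|---|
| Stated alternation, after the first allocation | 100% |
| Permuted blocks of 2, size known | (0.5 + 1) / 2 = 75.0% |
| Permuted blocks of 4, size known | (0.5 + 2/3 + 2/3 + 1) / 4 = 70.8% |
| Simple randomization | 50% |

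The block schemes are not in the article. They show that small blocks of known size remain partly guessable, which bears on the fix.

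**3. How many allocations are involved?** The article gives no count. If the group is the unit, and the group size of 3 to 8 given for DELTA before revision still applies (an assumption), 50 adolescents make between 50/8 = 6.25, about 7, and 50/3 = 16.7, about 17 groups. If the institution is the unit and some institutions supply several groups, there are fewer.

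**4. Where can selection enter the descriptive comparison?** Let w be the immediate arm's share of the analysed adolescents, D_I and D_W the mean baseline-to-follow-up changes in the immediate and waitlist arms, and P_W the mean PRE-to-baseline change in the waitlist arm. I read the Hypotheses section as comparing the pooled change with P_W:

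w × D_I + (1 − w) × D_W − P_W = (D_W − P_W) + w × (D_I − D_W)

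The first term compares two periods in the same arm and does not depend on allocation. The second is a between-arm difference weighted by w. With alternating clusters of similar size (an assumption), w is about 1/2. A difference between arms caused by selection would then pass into the comparison at about half its size. The article gives no figure from which that difference could be estimated.

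**5. Does another passage correct the label?** The closing remark in Study design is general and leaves the label standing. No section states a random start, a random order of institutions, an independent allocator or concealment. Recruiting before allocating, as in Sampling stage, does not conceal the next arm from an allocator who already knows it.

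**The case against.** The strongest reply is that the arms hardly matter here. The confirmatory test pools both arms, every adolescent is offered the intervention, and the article says openly that this is not a classical cluster-randomized trial. The natural-course comparison carries no test, and part of it is within the waitlist arm. Several of the listed confounders, such as housing, schooling and psychosocial support, belong to the shared setting, and with few clusters even true randomization would not secure balance.

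Most of this stands, and it limits the consequence. It does not justify the label, and it leaves the between-arm term in step 4 without a random basis. Institution and group might also mean the same thing if each institution supplies one group, but the article does not say so.

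Three stronger readings are tempting and not supported:

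- A reader might infer that institution staff, who approach the adolescents, can work out the arm before consent. The article does not say that they are told the sequence or what was allocated elsewhere. Only the principal investigator's foreknowledge follows from the text.
- A reader might infer that reordering one group shifts its share of the sample into the other arm. Under alternation, exchanging two neighbouring groups moves both, in opposite directions, and arm sizes change little. The risk lies in which groups land in which arm.
- A reader might infer that the primary result is biased by the allocation. Step 1 shows that it does not use it.

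**Conclusion.** The point holds as an error in the stated design. Allocation is deterministic and, as far as the article says, unconcealed, and it should not be called randomization. After the first cluster, every later arm is known to the allocator.

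The consequence is confined to three things: the randomized label wherever it appears, the comparability claim in Waiting list control group, and the immediate arm's part of the descriptive comparison, about half the weight if the arms are of similar size. The primary test and the sample size are untouched. The documents establish that selection could occur, not that it did. The conclusion rests on reading the sequence as literal alternation, which is how the article states it. The range of 7 to 17 groups rests on the pre-revision group size and serves only as a guide.

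**What to change.** For clusters not yet allocated, use a computer-generated sequence with varied, undisclosed block sizes, held by an existing team member outside recruitment. Release each arm once that cluster's participants have consented and before the week-0 assessment. It cannot wait until after that visit, because the visit is baseline in one arm and PRE in the other: Table 3 places intelligence and sociodemographics at baseline only, and Sampling stage sets payment at 20 EUR for baseline and 15 EUR for PRE.

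State one unit of allocation, institution or group, throughout. Report clusters already alternated as such; Setting and participants says that enrolment began on 2 February 2022, so some may exist.

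If the scheme is kept, call the allocation alternating and non-random wherever it is now called randomized. Drop or qualify the balance claim in Waiting list control group and the claim in Strengths and limitations that other explanations of time effects may be controlled for.

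The first route needs an amendment and a list, with no extra participants or staff. Its drawbacks are a mixed allocation scheme within one trial and a small chance imbalance in arm sizes. The second route costs only rewording.
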